### 3.2. Myotonometric Assessment

The mechanical properties of the paraspinal soft tissues were assessed using a MyotonPRO device (Myoton AS, Tallinn, Estonia). All measurements were performed by the same physiotherapist in the morning between 08:00 and 12:00 in the Body Posture Laboratory of the Jerzy Kukuczka Academy of Physical Education in Katowice, Poland. Participants were assessed in a relaxed prone position.

Measurement sites were selected according to the Fascial Manipulation concept described by Stecco and corresponded to the centers of coordination of the myofascial units involved in posterior trunk movement. The assessed regions represented the retro-collum (re-cl), retro-thorax (re-th), retro-lumbi (re-lu), and retro-pelvis (re-pv) myofascial units. Device settings, repetitions per site, calibration, averaging rules, and assessor reliability were not sufficiently documented to reconstruct and should not be inferred retrospectively.

Measurements were obtained bilaterally at sites corresponding to the C6, TH4, TH5, TH6, L1, and L5 spinal levels. At each level, the right side was assessed first, followed by the left side. A single measurement was obtained at each measurement site on each side by the same investigator.

The parameters analyzed in the present study were oscillation frequency (F, Hz), interpreted as an index of resting tissue tone, and dynamic stiffness (S, N/m), reflecting tissue resistance to deformation induced by a brief mechanical impulse.

### 3.3. Assessment of Respiratory Function

Respiratory function testing was performed by the same experienced investigator ([name]), a physiotherapist qualified to perform pulmonary function testing. Measurements were conducted in the morning between 08:00 and 12:00, with participants in a fasting state and at least 2 h after waking. Participants were instructed to avoid alcohol consumption and strenuous physical activity for 24 h before testing. Respiratory assessments were performed with participants in a seated position and using a nose clip where required by the respective measurement procedure. Oscillometry was performed before spirometry.

#### 3.3.1. Oscillometry

Respiratory system impedance was assessed using the Resmon PRO V3 system (RESTECH Srl, Milan, Italy) in accordance with current European Respiratory Society (ERS) technical standards [17]. Measurements were performed with participants seated and breathing quietly through a mouthpiece while wearing a nose clip. The cheeks and floor of the mouth were supported to minimize upper-airway shunting. Measurements were repeated only when the recording was technically invalid or unsuccessful. The parameters analyzed were respiratory system resistance at 5 Hz (R5), reactance at 5 Hz (X5), and resonant frequency (Fres).

#### 3.3.2. Spirometry

Spirometry was performed using an ultrasonic GANSHORN SpiroScout spirometer (GANSHORN Medizin Electronic GmbH, Niederlauer, Germany) in accordance with the American Thoracic Society/European Respiratory Society (ATS/ERS) acceptability and repeatability criteria [18]. Participants were assessed in a seated position using a nose clip. The best acceptable maneuver was used for analysis. The analyzed parameters were forced vital capacity (FVC), forced expiratory volume in 1 s (FEV1), the FEV1/FVC ratio, and forced expiratory flow at 50% of forced vital capacity (FEF50).

#### 3.3.3. Respiratory Muscle Strength

Respiratory muscle strength was assessed by measuring maximal inspiratory pressure (MIP) and maximal expiratory pressure (MEP) at the mouth using an RP Check respiratory pressure meter (MD Diagnostics Ltd., Maidstone UK). Measurements were performed with participants seated and results were expressed in cmH_2_O. The starting lung volumes, number of attempts, acceptance and repeatability criteria, and rule used to select the analyzed value were not documented in the contemporaneous materials available for this report. The measurements were performed, but these procedural details cannot be reconstructed reliably; this limits reproducibility, particularly for MIP as a registered primary clinical outcome.

#### 3.3.4. Lung Volumes and Gas Transfer

Lung volumes were assessed using the MiniBox system (PulmOne Advanced Medical Devices Ltd., Ra’anana, Israel). The assessed parameters included residual volume (RV) and total lung capacity (TLC). Gas transfer was additionally assessed using the single-breath diffusing capacity for carbon monoxide (DLCO/TLCO). Measurements were performed with participants in a seated position in accordance with the standardized pulmonary function testing procedure.

### 3.4. Sleep Polygraphy

Sleep-related respiratory parameters were assessed using the Nox T3 portable polygraphic system (Nox Medical, Reykjavík, Iceland). The examination was performed overnight in the participant’s home. Before the recording, each participant received detailed instructions regarding correct placement and use of the device and procedures intended to minimize interference with the recording. The system recorded airflow, respiratory effort, oxygen saturation, body position, and snoring. After completion of the overnight recording, the device was returned to the laboratory and the recorded data were analyzed by the same experienced investigator ([name]). Participants subsequently received an individual report of their examination. The available records do not document minimum valid recording duration, formal scoring rules, technical-failure handling, or scorer blinding; these omissions limit reproducibility.

### 3.5. Salivary Cortisol Assessment

Salivary cortisol concentration was assessed using morning saliva samples collected under fasting conditions. Participants provided saliva directly into three separate collection tubes. The samples were subsequently frozen and stored until biochemical analysis. Salivary cortisol concentration was determined using the SLV-2930 Salivary Cortisol ELISA assay (SLV-2930; DRG Instruments GmbH, Marburg, Germany). Laboratory analyses were performed at the Biochemistry Laboratory of the Institute of Sport Sciences, Jerzy Kukuczka Academy of Physical Education in Katowice, Poland. The same sampling procedure was applied at baseline and after the 8-week intervention period. Time relative to awakening, behavioural restrictions beyond fasting, medication and hormonal factors, storage temperature/duration, duplicate-assay reliability, detection limits, and a prespecified cortisol endpoint were not documented. A single morning sample at each time point cannot characterize chronic stress or the cortisol awakening response and is treated as exploratory.

## 4. Subjective Outcome Measures (Pre–Post)

Musculoskeletal symptoms were assessed using the Nordic Musculoskeletal Questionnaire (NMQ) across nine body regions: neck, shoulders, upper back, elbows, wrists/hands, lower back, hips/thighs, knees, and ankles/feet. NMQ-7 assessed symptoms during the previous 7 days and was treated as an exploratory pre–post symptom indicator. Because the six-month recall period extended substantially before the eight-week intervention, NMQ-6 was used only as descriptive contextual information concerning the broader history and anatomical distribution of symptoms and was excluded from analyses intended to represent change during the intervention. Binary symptom indicators were summarized using counts and proportions. The NMQ measures occurrence and distribution rather than symptom intensity.

Pain intensity was assessed separately using the Visual Analogue Scale (VAS). The scale ranged from 0 to 10, where 0 represented no pain and 10 represented the worst imaginable pain. Participants indicated the intensity of their perceived pain on the scale.

Psychological well-being was assessed using the World Health Organization Five Well-Being Index (WHO-5), a five-item self-report measure of subjective psychological well-being. Each item was scored from 0 to 5, resulting in a raw total score ranging from 0 to 25, with higher scores indicating better well-being. In the present study, the raw 0–25 score was used.

Health-related quality of life was assessed using the 36-Item Short Form Health Survey (SF-36). The questionnaire evaluates eight domains: physical functioning, role limitations due to physical health, bodily pain, general health perceptions, vitality, social functioning, role limitations due to emotional problems, and mental health. Higher domain scores indicate better health-related quality of life.

### 4.1. Description of Interventions

The study included two distinct non-pharmacological interventions: craniosacral therapy (CST) and respiratory training (RT). The interventions were delivered independently and were not combined within a single treatment arm. The control group (CG) did not receive either study intervention during the 8-week study period. The planned exploration comparisons included CST versus CG, RT versus CG, and CST versus RT. These comparisons were intended to generate preliminary estimates of potential between-group differences rather than to provide confirmatory evidence of comparative effectiveness.

#### 4.1.1. Craniosacral Therapy (CST)

Craniosacral therapy (CST) was delivered individually in a one-to-one therapist–participant format once weekly for 8 consecutive weeks, resulting in a total of eight sessions per participant. Each session lasted approximately 60 min. All sessions were delivered by the same physiotherapist ([name]), a certified CST therapist, according to the same standardized intervention protocol throughout the study.

CST was based on gentle, non-invasive manual contact, described within the therapeutic approach as a “butterfly touch”, corresponding to approximately 5 g of applied force. The intervention involved gentle perceptual tactile contact intended to promote relaxation and a state of balanced tissue tension. No manual mobilization or manipulation techniques were performed. The intervention was standardized rather than individually tailored. Missed-session rescheduling, co-intervention restrictions, a formal fidelity checklist, and procedures to reduce therapist allegiance were not documented and are not added retrospectively.

Sessions were conducted between 12:00 and 21:00 in the same treatment setting using a therapy table. Participants remained comfortably dressed and rested in a relaxed supine position with the head supported by a pillow; a blanket was provided when required. Before the intervention, participants were informed that sensations of warmth or cold of varying intensity might occur during the session, although the intervention could also proceed without any particular sensory sensations.

Each session followed the same predefined sequence of therapist hand placements. The intervention began at the feet and subsequently involved the sacrum, lumbar region, diaphragm, superior thoracic aperture, cranial base around the foramen magnum, occipital region, temporal bones, frontal bone, and sphenoid bone, followed by completion of the session. The same sequence was applied to all participants during each of the eight sessions.

Following each session, participants were provided with mineral water and advised to maintain adequate hydration. They were also informed that transient emotional responses, such as irritability, could occur following the intervention. Participants were instructed to contact the therapist if such symptoms persisted for more than 72 h or at any time if they experienced concerns related to the intervention.

#### 4.1.2. Respiratory Training Program (RT)

Participants in the respiratory training group completed an 8-week home-based respiratory training program comprising resistive inspiratory muscle training (IMT), controlled breathing exercises, and breathing exercises combined with spinal movement. Inspiratory muscle training was performed using a POWERbreathe Plus device (POWERbreathe International Ltd., Southam, UK). Participants completed two sessions of 30 inspiratory efforts per day. Training resistance was individualized and progressively increased by one-quarter turn of the resistance adjustment knob once the participant was able to complete 30 consecutive inspirations without interruption. The precise baseline resistance/load, reassessment schedule, total duration of the slow-breathing component, and formal stopping criteria were not documented; the device and breathing elements should therefore be interpreted as a multicomponent program whose component-specific effects cannot be separated.

Before beginning the program, participants received instruction on the correct use of the device. The first three training sessions were supervised remotely, after which training was performed independently at home. Participants maintained training diaries documenting completion of the prescribed sessions, any symptoms experienced during training, and increases in training resistance.

Controlled breathing exercises consisted of a slow nasal inspiration, a brief breath hold of approximately 1–2 s, and a prolonged expiration, with a target inspiratory-to-expiratory time ratio of approximately 1:2. The exercises were performed in either a seated or quadruped position, with emphasis on lower-rib expansion, typically in sets of 5–10 repetitions. In the quadruped position, breathing was additionally combined with alternating spinal flexion and extension. No adverse events related to the respiratory training program were reported during the 8-week intervention period.

The amount and mode of therapist contact differed between the intervention groups. Participants in the CST group received eight individual, approximately 60 min face-to-face sessions with the same therapist, whereas the RT program was primarily home-based, with the first three training sessions supervised remotely and subsequent sessions performed independently. The control group received neither study intervention. Because of the nature of the interventions, participants could not be blinded to group allocation, and no attention-matched or sham control condition was used.

#### 4.1.3. Control Group (CG)

Participants in the control group did not receive any intervention during the study period,In accordance with ethical principles, participants were informed about the opportunity to receive one of the therapeutic interventions after completion of the project.

### 4.2. Statistical Analysis

Statistical analyses were performed in R 4.3.2 after study completion. The primary quantities of interest were the feasibility proportions for recruitment, consent, retention, attendance/adherence, and outcome completeness. Clinical analyses were secondary and exploratory. The target exploratory contrasts were CST versus CG, RT versus CG, and CST versus RT for change from baseline to 8 weeks. The analyses estimated differences in observed change among participants as allocated; no causal estimand was prespecified, and the non-randomized design leaves residual confounding. The principal clinical analyses used change scores because these were the analyses conducted before revision. Baseline-adjusted or mixed models were not represented retrospectively as prespecified analyses.

For each outcome, change scores were calculated as the difference between the post-intervention and baseline values (Δ = post-intervention value − baseline value). The distribution of change scores was assessed using the Shapiro–Wilk test.

Within-group pre–post comparisons were performed using paired Student’s t-tests for variables meeting the normality assumption and Wilcoxon signed-rank tests for variables that did not meet this assumption. These tests described temporal change within groups and were not interpreted as evidence of an intervention-specific effect. Between-group differences in change scores were assessed using the Kruskal–Wallis test. When the overall test indicated a difference (*p* < 0.05), pairwise Mann–Whitney U comparisons were performed for CST versus RT, CST versus CG, and RT versus CG. Binary NMQ symptom indicators were summarized as counts and proportions rather than analyzed as continuous change scores.

For salivary cortisol, for which the assumptions for parametric analysis were met, within-group changes were assessed using paired Student’s *t*-tests, while between-group differences in change scores were assessed using one-way analysis of variance (ANOVA), followed by Tukey’s post-hoc test where appropriate.

To account for multiple comparisons within related outcome families, Holm adjustment was applied separately to the family of sleep-related outcomes and to the family of spirometric and oscillometric outcomes. No multiplicity adjustment was applied across the complete set of exploratory clinical outcomes; consequently, unadjusted *p*-values outside these families are descriptive and not confirmatory.

Effect sizes were calculated to complement statistical significance testing. Standardized mean change was calculated as d = mean(Δ)/SD(Δ), and rank-biserial correlation (r) was calculated where appropriate. Effect estimates and 95% confidence intervals are intended for the reporting of clinical results, where supported by the corresponding estimators. No clinical outcome results are presented in this protocol report. Given the small sample, all clinical estimates and *p*-values were interpreted cautiously and within an exploratory framework. No confounder-adjusted model or formal sensitivity analysis was prespecified; additional complex models were not introduced retrospectively. Age and baseline outcome value are identified as priorities for a future adequately powered trial.

All 32 enrolled participants contributed to the feasibility analysis and completed 8-week outcome assessment; no pre-post values were missing. The analysed clinical sample therefore equalled the full enrolled sample. No imputation, per-protocol exclusion, outlier exclusion, treatment-discontinuation analysis, or missing-data sensitivity analysis was required or performed.

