### 1.3. Study Objectives

The primary objective of this pilot and feasibility study was to assess the feasibility and acceptability of implementing two non-pharmacological interventions—craniosacral therapy (CST) and respiratory training (RT)—in mothers of children with disabilities. Feasibility and acceptability were considered in relation to recruitment and retention, intervention attendance and adherence, completeness of outcome assessments, intervention fidelity, withdrawals, and adverse events.

A secondary objective was to obtain preliminary estimates of potential changes in participants’ psychological well-being and health-related quality of life and to explore differences between the craniosacral therapy, respiratory training, and control groups. The registered primary clinical outcomes were spinal mobility assessed using the IDIAG M360 system and respiratory function assessed using maximal inspiratory pressure (MIP). Secondary clinical outcomes included salivary cortisol concentration, myotonometric measures of tissue tone and stiffness, musculoskeletal symptoms, health-related quality of life assessed using the 36-Item Short Form Health Survey (SF-36), and psychological well-being assessed using the World Health Organization Five Well-Being Index (WHO-5). Musculoskeletal complaints and pain, as well as biomechanical, respiratory, sleep-related, and biochemical measures, were considered secondary or exploratory outcomes.

Given the pilot nature of the study and its limited sample size, analyses of clinical outcomes were intended to provide preliminary estimates of intervention effects and their corresponding confidence intervals rather than confirmatory evidence of intervention effectiveness. These preliminary findings were intended to inform the design, selection of outcomes, and methodological procedures of a future adequately powered randomized controlled trial.

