### 2.4. Group Allocation and Choice of Comparators

A total of 45 mothers were assessed as eligible; 13 declined before allocation and 32 consented and entered the study. Participants were allocated to CST (*n* = 12), RT (*n* = 10), or CG (*n* = 10). The active groups represented two distinct non-pharmacological approaches; they were not combined. The no-intervention control provided a pragmatic comparator, although it did not control for attention or expectation.

Allocation was non-randomized. The principal investigator assigned participants according to enrolment sequence and the project delivery schedule: earlier enrollees entered CST so that eight weekly therapist-delivered sessions could be completed within the grant period; later enrollees entered RT or CG according to remaining capacity. Allocation was not based on baseline outcomes, but this procedure could still create selection bias and confounding. Participants, the CST therapist, most outcome assessors, and the analyst were not blinded; respiratory tests were performed by a separate investigator who was also not documented as blinded.

The intervention period lasted 8 weeks, after which the post-intervention assessment was performed. All assessments were conducted in the morning at the laboratories of the Jerzy Kukuczka Academy of Physical Education in Katowice, Poland. For each participant, all measurements were completed within a single day and were performed in an order intended to minimize the potential influence of fatigue. Participant flow through the study is presented in Figure 1.

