### 2.5. Sample Size

No formal priori sample size calculation was performed because the study was designed as a pilot and feasibility project conducted within the framework of a time-limited institutional mini-grant. The sample size was therefore determined pragmatically based on recruitment feasibility, available project resources, and the capacity to deliver the interventions within the project timeframe. In particular, the CST intervention required eight individual 60 min sessions per participant, delivered once weekly over eight consecutive weeks by the same therapist, which limited the number of participants who could feasibly complete the intervention during the funding period. The final sample comprised 32 participants: 12 in the CST group, 10 in the respiratory training group, and 10 in the control group. Accordingly, the study was not powered to provide confirmatory evidence of intervention effectiveness, and analyses of clinical outcomes should be interpreted as exploratory.

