Registered primary clinical	Spinal mobility; MIP	IDIAG M360; RP Check	Baseline and 8 weeks	Exploratory pre–post and between-group estimates
Secondary/exploratory	Myotonometry, spirometry/oscillometry, lung volumes/gas transfer, sleep polygraphy, cortisol, WHO-5, SF-36, NMQ-7 (exploratory pre–post), NMQ-6 (descriptive context), VAS	Specified instruments	Baseline and 8 weeks	Exploratory; direction depends on measure

**Table 4 healthcare-14-03093-t004:** Summary of intervention and control conditions.

Group	Mode	Dose	Delivery/Progression	Monitoring
CST	1:1, face-to-face	8 × ~60 min; weekly	Certified CST physiotherapist; standardized hand-placement sequence	Attendance record; same provider/protocol
RT	Home-based multicomponent IMT + slow breathing + spinal movement	2 × 30 inspirations/day plus exercises; 8 weeks	POWERbreathe Plus; first 3 sessions remotely supervised; diary; resistance +1/4 turn after 30 uninterrupted inspirations	Diary sessions, symptoms, resistance
CG	No intervention	8 weeks	Usual activities; intervention offered after project	No attention matching

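### The three target between-group contrasts are tested only after Kruskal–Wallis p < 0.05, and no ungated between-group estimator with an interval is named, although the stated aim is estimation

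*Protocol article*

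**What the plan says.** Section 1.3 gives the purpose of the clinical analyses: "analyses of clinical outcomes were intended to provide preliminary estimates of intervention effects and their corresponding confidence intervals rather than confirmatory evidence". Section 4.1 says the same of the three pairwise comparisons, and Table 3 lists "Exploratory pre–post and between-group estimates" as the analysis for the registered primary clinical outcomes.

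Section 4.2 then names the quantities of interest: "The target exploratory contrasts were CST versus CG, RT versus CG, and CST versus RT for change from baseline to 8 weeks". The procedure for them has two steps. First, "Between-group differences in change scores were assessed using the Kruskal–Wallis test". Second, "When the overall test indicated a difference (*p* < 0.05), pairwise Mann–Whitney U comparisons were performed" for the three pairs.

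Two kinds of outcome fall outside this route. Salivary cortisol has ANOVA, with Tukey's test to follow when suitable. Binary NMQ indicators are summarised as counts and proportions.

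The end of Section 4.2 defines a standardised mean change, d = mean(Δ)/SD(Δ), and adds a rank-biserial r for use when suitable. It also says that estimates and 95% intervals are meant to be reported wherever the estimators allow.

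**The concern.** An omnibus rank test across three arms estimates none of the three contrasts. The step that does address them runs only after a significant result, in a study that says of itself that "the study was not powered to provide confirmatory evidence of intervention effectiveness". A quantity named as a target should not depend on a p-value for its existence.

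The effect sizes in Section 4.2 do not clearly fill the gap. The d defined there divides the mean change by the SD of change, so it describes change and not a difference between arms. Rank-biserial r could serve a between-arm comparison, but it is not assigned to one, has no stated interval, and could itself be computed only once the gate has opened. The Shapiro–Wilk branch steers the within-group tests only.

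The article expects the data to help identify responsive outcomes and plan the next trial's sample size (Sections 1.2 and 8). Estimates that survive a p < 0.05 filter with 10 to 12 women per arm are the wrong input for both.

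**Working it through.** The documents give no operating characteristic for this rule, so there is no figure of theirs to reproduce. The check is a simulation of the rule as written.

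**Inputs from the article**
- Arm sizes 12, 10 and 10, N = 32 (Section 2.4).
- Complete data: "no pre-post values were missing" (Section 4.2).
- Gate: Kruskal–Wallis on change scores, p < 0.05 (Section 4.2).

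**Assumptions, not in the article**
- Change scores are normal with SD 1 in each arm.
- True differences range from 0 to 1.0 SD. No effect size or SD of change is given, so a range is shown.

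**Formulas**
- H = 12/(N(N+1)) × Σ(R_j²/n_j) − 3(N+1), where R_j is the rank sum of arm j. The gate opens when the chi-square (2 df) p-value is below 0.05, that is, H > −2 ln 0.05 = 5.99.
- D = mean change in CST − mean change in control, with interval D ± t(0.975, 20) × √(s₁²/12 + s₂²/10).

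**Results (40,000 simulated trials per row)**

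| True effect (SD) | Gate opens | Mean D, all trials | Mean D, gate open | Ratio to truth | 95% CI coverage, gate open |
|---|---|---|---|---|---|
| None | 4.6% | 0.00 | 0.00 | – | 51% |
| CST only 0.2 | 6.7% | 0.20 | 0.61 | about 3 | 60% |
| CST only 0.5 | 18.0% | 0.50 | 0.94 | 1.9 | 85% |
| CST only 0.8 | 40.8% | 0.80 | 1.10 | 1.4 | 93% |
| CST only 1.0 | 59.9% | 1.00 | 1.20 | 1.2 | 95% |
| Both active arms 0.5 | 16.3% | 0.50 | 0.96 | 1.9 | 84% |
| Both active arms 0.8 | 37.7% | 0.80 | 1.13 | 1.4 | 93% |
| CST 0.5, RT 0.25 | 13.8% | 0.50 | 1.03 | 2.1 | 81% |

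With no true effect, the average absolute D rises from 0.34 over all trials to 0.73 when the gate opens. The rank-biserial r behaves in the same way: for CST only at 0.5 SD its mean goes from 0.27 to 0.53.

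Over all trials, without the gate, D is unbiased and coverage is about 95% in every row.

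**What this would do to planning.** Sample size scales with 1/effect². Planning on 0.94 when the truth is 0.50 gives (0.50/0.94)² = 0.28, or about 28% of the number needed.

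**Precision without the gate.** In units of the SD of change, the half-width is t × √(1/n₁ + 1/n₂):
- 12 versus 10: 2.086 × 0.428 = 0.89.
- 10 versus 10: 2.101 × 0.447 = 0.94.

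**The case against.** The strongest reply is that the gated sentence concerns tests. Nothing in Section 4.2 says that estimates or intervals depend on the Kruskal–Wallis result. The section says that differences in change were estimated, and it states separately an intention to report estimates and 95% intervals. Table 3 lists between-group estimates without condition. The exact shift estimator is also a detail that an article may leave to a fuller plan.

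Much of this stands. A reader might infer that most outcomes will have no between-group estimate and that those reported are inflated. The documents do not support that as a statement of fact. They gate the tests and not expressly the estimates, rank-biserial r is named, and cortisol and the binary NMQ indicators lie outside the Kruskal–Wallis route. How often the gate opens, and by how much estimates inflate, depends on true effects that nobody has stated. At 1.0 SD the gate opens in 60% of trials and the inflation is only 1.2 times.

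Two further points count against a blunt remedy. Section 4.2 describes, in the past tense, analyses already run, so striking out the gate would erase a true record. The omnibus step also gives the pairwise tests some protection against multiplicity, which matters because Holm adjustment covers only two outcome families.

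What the reply does not remove is the mismatch. The article states the aim as estimates with intervals for three contrasts, and the only between-group procedure it spells out for spinal mobility, MIP and most other outcomes is a significance filter.

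**Conclusion.** The conflict between the estimation aim and the conditional procedure is in the text and needs no assumption. Outside cortisol, no ungated between-group estimator with an interval is named for the continuous outcomes.

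The size of the harm is conditional. It arises only if reported estimates follow the gate, and the figures rest on normal change scores with equal SD. On those terms, for a CST-only effect between 0.2 and 1.0 SD, a contrast would be available in about 7% to 60% of cases, and the CST–control estimate would be overstated by a factor of about 3 down to 1.2.

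This should be fixed but is not critical. Feasibility proportions are the primary quantities, the clinical analyses are declared exploratory, and the article presents no clinical results, so no published estimate is yet affected. Removing the selection would not remove the confounding that comes with non-random allocation, which the article acknowledges.

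**What to change.** Keep the description of the Kruskal–Wallis and Mann–Whitney steps as conducted. Add to Section 4.2 that:
- for every continuous outcome, all three contrasts in change are reported with 95% confidence intervals, whatever the omnibus p-value;
- one named estimator is used throughout, for example the Hodges–Lehmann shift, which matches the Mann–Whitney test, so that no choice between estimators is left open now that the data are known;
- the Kruskal–Wallis p-value is descriptive;
- this reporting rule was adopted after data access.

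The cost is a few sentences and a short re-run on 32 complete cases. It adds none of the complex models that the article declines to introduce. There are two downsides. The intervals will be wide, with a half-width of about 0.9 SD of change. The pairwise comparisons also lose the partial multiplicity protection of the omnibus step, so they must be presented as descriptive.
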